**Methods:**

This protocol describes a longitudinal, nonrandomized controlled trial, with baseline, 3 month, and 6-month follow-up assessments. The intervention consisted of using the web-based CoEd application for 3 months to 6 months. This application is composed of a child’s file in which stakeholders of the support team can share information about the child’s profile, skills, aids and adaptations, and daily events. The control group is asked to function as usual to support the child in inclusive settings. To be eligible, a support team must be composed of at least two stakeholders, including at least one of the parents. Additionally, the pupil had to be aged between 10 years and 16 years, enrolled in secondary school, be taught in mainstream settings, and have an established or ongoing diagnosis of autism spectrum disorder, attention-deficit/hyperactivity disorder, or intellectual disability (IQ<70). Primary outcome measures cover stakeholders’ relationships, self-efficacy, and attitudes toward inclusive education, while secondary outcome measures are related to stakeholders’ burden and quality of life, as well as children’s school well-being and quality of life. We plan to analyze data using ANCOVA to investigate pre-post and group effects, with a technological skills questionnaire as the covariate.

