### Outcome Measures

#### Selection of Outcome Measures

Outcome measures were chosen from the researchers’ hypotheses and participatory decision-making. In 2 focus groups, parents, teachers, and health care professionals discussed the CoEd application’s potential impact and evaluation criteria (Multimedia Appendix 2). Participants reviewed preselected indicators and suggested new measures, especially concerning quality of life and caregiver burden, for the field study. As a result, the primary outcomes include 3 main dimensions (ie, stakeholders’ relationships, perceived individual efficacy, and attitudes toward school inclusion). To this end, parents, teachers, and health care professionals completed a series of common or specific questionnaires (Table 1). The secondary outcomes include measures for stakeholders (burden and quality of life) and for the children (quality of life, school well-being, and school inclusion perception; Table 1). Additionally, a measurement of technology experience that covers technology skills and CoEd experience was included for the intervention group (Table 1). Although some questionnaires had a validated French version, others did not. In the latter case, as we are French native speakers, we translated them in collaboration with native English speakers. The scales used are presented in Table 1.

**Table 1 table1:** Description of the assessment batteries to address the targeted (primary and secondary) outcomes and technology experience of participants.

Outcomes, dimension, and subdimension				Questionnaire		Respondent						
						Child		Parent		Teacher		Professionals

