	**CoEd** **application experience**											
		Subjective user experience	User Experience Questionnaire, short version and Technology-based Experience of Need Satisfaction (TENS)^a^		—		X		X		X	
		Objective user experience	The uses and usages of the CoEd application are quantified with the following indicators across periods of 3 months or 6 months: (1) number of times the application is opened and (2) number of exchanged posts		—		X		X		X	

^a^Translated in French by the authors.

^b^Not applicable.

^c^Intervention group only.

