##### Measurement of Technology Experience (Experimental Group Only)

To assess the potential effect of prior technology skills on the use of CoEd, parents and professionals completed the Computer Usage Questionnaire [56] that consists of a self-reported measure of 18 questions asking for the frequency (5-point scale ranging from never to very often) of different computer activities and software usage.

To address the specific user experience with the CoEd application, the User Experience Questionnaire short form [57] was selected as the measurement. It uses a 7-point Likert scale (–3=fully agree with negative term to +3=fully agree with positive term) of subjective perceptions of users in terms of both the hedonic and pragmatic dimensions toward a given product and according to a benchmark for digital products. The Technology-based Experience of Need Satisfaction-Interface [58] is related to the self-determination theory framework for assessment and uses a 5-point Likert scale (1=Do Not Agree to 5=Strongly Agree) to assess basic psychological need (autonomy, competence, relatedness) satisfaction through the interaction with the interface or system. Satisfaction of these needs is arguably associated with sustained engagement with a technology.

Complementary to the subjective measures, direct measures of CoEd use and usage are collected through active interactions (log data) with this web application, in particular the number of times the app was opened and the number of exchanged posts (Table 1).

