#### Planned Statistical Analyses

We plan to conduct pre-post mean comparison analysis on primary (RQ1) and secondary outcomes (RQ2 and RQ3) to assess within and between-team effects of the intervention. We will conduct within-team analyses using 1-way ANCOVA to compare pre and postintervention differences separately for each team’s experimental and control groups. This approach helps identify specific changes within teams and assesses differential effects between groups. Additionally, a between-team analysis will treat all participants as a single population, using repeated-measures ANCOVAs or linear regression analyses to examine the overall intervention effect across teams. This global analysis disregards team distinctions to assess the intervention’s overall impact. In addition, using ANCOVA will allow us to control for potential bias coming from the variability in technological skills (Computer Usage Questionnaire; see Table 1) as well as any variable that may compromise the homogeneity across groups. Missing data will result in the exclusion of related observations, and dropouts will be monitored to explore the reasons.

By combining these methods, we aim to provide a comprehensive evaluation of the psychological intervention’s effectiveness, considering both within-team variation and overall effects.

To assess the user experience (RQ4), only the participants of the CoEd intervention condition answered the user experience questionnaire. These data will be analyzed through descriptive statistics and compared with questionnaire-related benchmarks.

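### The one covariate named for the group comparison, the Computer Usage Questionnaire, is recorded in the intervention arm only, so it cannot adjust that comparison

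*Protocol article*

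**What the plan says.** The article names one specific covariate. The abstract says: "We plan to analyze data using ANCOVA to investigate pre-post and group effects, with a technological skills questionnaire as the covariate". The Planned Statistical Analyses section identifies the instrument and gives its purpose: "using ANCOVA will allow us to control for potential bias coming from the variability in technological skills (Computer Usage Questionnaire; see Table 1"). The same sentence goes on to cover any other variable on which the groups turn out to differ, so the questionnaire is offered as protection against between-group bias. The overall model is one in which "a between-team analysis will treat all participants as a single population, using repeated-measures ANCOVAs or linear regression analyses" are used. The Discussion (Strengths and Limitations) repeats that the technological skills questionnaire will be a covariate.

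Three places state who completes it:

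- Selection of Outcome Measures: "a measurement of technology experience that covers technology skills and CoEd experience was included for the intervention group".
- Table 1: the Technology experience block, which holds the Computer Usage Questionnaire row, carries footnote c, which reads "Intervention group only".
- The subsection that describes the questionnaire is headed "Measurement of Technology Experience (Experimental Group Only").

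On missing data, the analysis section says: "Missing data will result in the exclusion of related observations". It makes no exception for covariates.

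**The concern.** The article prescribes a covariate for the group comparison and also says that the covariate exists in only one of the two groups. Both statements cannot be acted on together. This is not a detail left to a separate analysis plan, because the article itself fixes both the covariate and its respondents.

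The stakes are higher than in a randomised trial. Allocation followed recruitment and was not random, so the comparison leans on covariate adjustment, and this is the only adjustment variable the article names. An analyst who follows the text gets no group effect. One who departs from it must choose another covariate set, possibly with outcome data in hand. Readers would also be told that differences in computer skill between groups had been controlled when they had not.

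**Working it through.** The article gives no figure for this point that could be reproduced. The question is whether the group effect can be estimated.

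**Inputs.** Results section, after baseline: 82 participants in 13 CoEd teams and 45 participants in 11 control teams. Check: 82 + 45 = 127 participants, as stated in the abstract; 13 + 11 = 24 teams.

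**Step 1, complete cases.** With the questionnaire in the model and observations with missing data excluded:

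- CoEd: at most 82 of 82 kept.
- Control: 0 of 45 kept.
- Loss: 127 − 82 = 45 participants, and 45/127 = 35%. In teams, 11 of 24.

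**Step 2, estimability.** Take the model

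outcome = b0 + b1 × group + b2 × questionnaire + b3 × baseline outcome.

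Among the remaining rows group = 1 throughout, so the group column equals the intercept column. A design matrix built with 82 CoEd rows, and 45 control rows lacking the questionnaire, had rank 3 for 4 columns after deletion. Only the sum b0 + b1 is identified; b1 is not.

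**Step 3, the separate analyses by group.** The plan also has one-way ANCOVAs run separately for the experimental and control groups. With the questionnaire as covariate, the control analyses would have no usable rows. The CoEd analyses could run.

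**Step 4, filling in the controls instead of deleting them.** Suppose each control is given a constant value f. Leaving the baseline term aside, the adjusted difference is

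b1 = (mean outcome CoEd − mean outcome control) − b2 × (mean questionnaire CoEd − f).

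Each unit added to f moves b1 by b2, and no control data bear on f. In a simulated data set (82 and 45 participants, group effect set to 0.6, questionnaire slope 0.5 in the CoEd arm):

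| Fill value f | Estimated group effect |
|---|---|
| −1 | −0.05 |
| 0 | 0.45 |
| 1 | 0.95 |
| 2 | 1.45 |

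The change is 1.45 − (−0.05) = 1.50 over 3 units, or 0.50 per unit, which is the slope. The estimate reflects the chosen fill value. A more elaborate imputation has the same weakness, because missingness coincides exactly with group.

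**Step 5, without the covariate.** In the same simulated data, the model with group and baseline outcome used all 127 rows and returned a group estimate (0.45, standard error 0.17). The obstacle is the questionnaire alone.

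**The case against.** The best counter-argument is that the restriction to one arm may be a labelling slip. The sentence describing the questionnaire says that parents and professionals completed it, without mentioning an arm, and it measures prior skill, which could be asked of anyone. The analysis section says explicitly that only CoEd participants answered the user experience questionnaire, and puts no such limit on the Computer Usage Questionnaire. This reading cannot be excluded. It is the weaker one, since three separate statements go against it, and if it is right those three statements are wrong.

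A second argument is that the covariate was meant for use within the CoEd arm. The Discussion does speak of skill variability in that condition, and such an analysis is feasible. But the abstract ties the covariate to group effects and the analysis section ties it to control of bias.

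Third, the deletion rule stands next to a remark on dropouts and may not have been written with a questionnaire withheld by design in mind. That affects the count of excluded controls but not the conclusion: steps 2 and 4 show that the adjustment fails whether controls are deleted or filled in.

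Fourth, 127 is a count after baseline and not an analysis set. This is correct. The article reports 89 participants at 3 months and 67 at 6 months without a split by arm, so the 35% should not be read as the share lost at follow-up. The loss is the whole control arm at any time point.

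**Conclusion.** The concern holds. As written, any between-group model containing the Computer Usage Questionnaire has no estimable group effect, and the claim that ANCOVA removes between-group bias from technological skill has no data behind it. The size is 100% of the control arm: 45 of 127 participants and 11 of 24 teams, on post-baseline counts.

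This assumes that the three statements restricting the questionnaire to the intervention group are accurate, and the exact counts also assume that the exclusion rule applies to covariates. If the first assumption fails, the error lies in those three statements. If the second fails, the adjustment is still impossible. Group comparisons without this covariate, and analyses within the CoEd arm that use it, are unaffected.

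A related gap: Table 1 lists no child respondent for the questionnaire, so child-reported outcomes have no score from the same respondent in either arm.

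**What to change.** Begin by checking the data. Collection ended in June 2024, so the authors already know whether controls have questionnaire scores.

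- **If controls have none:** take the questionnaire out of every between-group model and out of the control-group ANCOVAs. List in advance the covariates available in both arms, such as baseline outcome score, respondent role, team size and the child's diagnosis. Keep the questionnaire for analyses within the CoEd arm, as a modifier of pre-post change and of logged use. Amend the abstract, the Planned Statistical Analyses section and the Discussion sentence, and withdraw the claim that skill bias between groups is controlled.
- **If controls completed it:** correct the sentence in Selection of Outcome Measures, footnote c of Table 1 and the subsection heading, and say when the questionnaire was given. The planned adjustment can then stand for adult-reported outcomes.

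In both cases, fix the covariate list before outcomes are compared between groups; if that comparison has already been made, report the date of the decision. The cost is wording and model specification, with no new data. In the first case the adjustment of the group comparison for computer skill is given up, and unmeasured skill differences should be listed as a limitation.

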##### Child’s Perception of School Life

The student's sense of school inclusion was evaluated using the single-item inclusion scale by Aron et al [53], which measures 7 levels of the sense of inclusion and has been adapted to assess the sense of inclusion in both the school and peer group contexts. School satisfaction was evaluated using an 8-item subscale that uses a 7-point Likert scale (1=strongly disagree to 7=strongly agree) derived from the French adaptation of the Multidimensional Students’ Life Satisfaction Scale [54,55].

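### The named ANCOVA covariate is never collected from children and exists only in the intervention arm, so no child quality-of-life or school-life measure has an estimable adjusted group comparison as written

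*Protocol article*

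**What the plan says.** Planned Statistical Analyses sets the scope: "We plan to conduct pre-post mean comparison analysis on primary (RQ1) and secondary outcomes (RQ2 and RQ3". The same paragraph gives the reason for ANCOVA, that "using ANCOVA will allow us to control for potential bias coming from the variability in technological skills", and names the Computer Usage Questionnaire. The abstract's Methods paragraph repeats the choice, "with a technological skills questionnaire as the covariate", and exempts no outcome. For incomplete data the rule is "Missing data will result in the exclusion of related observations".

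On who supplies the covariate, the measurement section says that "parents and professionals completed the Computer Usage Questionnaire". Table 1 agrees: parents, teachers and professionals are ticked, and the child cell is marked not applicable.

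On which arm supplies it, three places agree. The section heading reads "Measurement of Technology Experience (Experimental Group Only" (closing bracket omitted here). Selection of Outcome Measures says that "a measurement of technology experience that covers technology skills and CoEd experience was included for the intervention group". Footnote c of Table 1 limits the whole technology block to the intervention group.

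The child measures are secondary outcomes in Table 1. The PedsQL has a child self-report and a parent proxy. The other two are answered by the child alone: school satisfaction ("School satisfaction was evaluated using an 8-item subscale") and the single-item school inclusion scale.

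**The concern.** The article fixes an outcome scope, a covariate and a deletion rule, and for the child measures the three do not work together. The children cannot have a value of the covariate in either arm. The parents who give the proxy report have one only in the intervention arm.

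At stake is whether the trial can report an adjusted controlled result on the child's quality of life and school life, which form part of RQ3 and bear on the benefit to the child. If the plan stays as it is, the analyst must improvise. One route is to drop the covariate for some outcomes; the other is to lend the child the score of an adult in the team. Teams had 2 to 7 people at recruitment, so the second route leaves the choice of adult open. Data collection ended in June 2024 and analysis began in March 2025, so any such choice would be made with the outcome data in hand.

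**Working it through.** The plan states no figure for this point, so there is nothing to reproduce. The check is a count of complete cases by respondent and arm.

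**Inputs**
- Teams after baseline: 13 CoEd and 11 control (Results).
- Participants: 82 CoEd and 45 control, 127 in all (Results).
- Covariate available: adults yes, children no (Table 1; Measurement of Technology Experience).
- Covariate available: CoEd arm yes, control arm no (the three places cited above).
- Deletion rule: records with missing data are excluded (Planned Statistical Analyses).
- Assumption: one child and one responding parent per team. The article does not report the number of child respondents.

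**Formula.** Usable records in an arm = respondents in that arm × c, where c is 1 if the covariate was collected for that respondent type in that arm and 0 otherwise.

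| Outcome and covariate source | CoEd | Control |
|---|---|---|
| Three child-reported measures, child's own value | 13 × 0 = 0 | 11 × 0 = 0 |
| Parent-proxy PedsQL, parent's own value | 13 × 1 = 13 | 11 × 0 = 0 |
| Child-reported measures, parent's value lent to the child | 13 × 1 = 13 | 11 × 0 = 0 |

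In the first row no model can be fitted. In the other two rows the group indicator takes a single value in the retained data, so it cannot be separated from the intercept and the adjusted group effect is not estimable.

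**If control adults also had the questionnaire.** The parent-proxy row would become 13 v 11. The first row would stay at 0 v 0, because no child completes the questionnaire in either arm. The third row would become 13 v 11, but it depends on a rule for linking child to adult that the article does not state. Filling the control arm therefore does not by itself repair the child-reported models.

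**Reach beyond the child measures.** The same deletion removes every control participant from any group comparison adjusted for this covariate: 45 / 127 = 35% of the sample, adult primary outcomes included.

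**The case against.** The strongest reply is that a cell marked not applicable is not missing data, so the deletion rule need not apply. The article never says that a child's model uses the child's own score, and a condensed article may leave the covariate set for each outcome to a fuller document. Part of this stands: total loss of records is the literal reading, not a consequence the article states. But the point does not rest on absent detail. The stated scope, covariate and deletion rule conflict, and even on the lenient reading the covariate for child-reported outcomes is undefined.

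A second reply is that an adult's computer skill is a plausible modifier of the child's result. The Strengths and Limitations section expects skills to modulate the effect and expects benefit to reach the child through collaboration. That is fair, and the covariate should not be called irrelevant. Plausibility does not supply control-arm values, however, and does not say which adult's score to use.

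A third reply is that this merely follows from the covariate being absent in the control arm. That is largely so if the questionnaire is dropped from every group comparison. It is not so if the repair is to obtain it from control adults.

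Two stronger readings should be resisted:
- A reader might infer that the child evidence would then rest on the parent proxy alone. The documents do not support this. Control parents have no covariate value either, so the proxy does not survive as an adjusted controlled comparison. Parents, teachers and professionals also rate the child's goals on the Goal Attainment Scale, which bears on RQ2 although Table 1 lists it as a primary stakeholder outcome.
- A reader might also cite the low power of 13 v 11 children as the size of the defect. That limitation is the same whatever the covariate, and it does not measure this problem.

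**Conclusion.** The point holds in this form. As written, the adjusted model has no usable records for three child-reported measures and no control arm for the fourth child measure, the parent-proxy PedsQL. No child quality-of-life or school-life measure therefore has an estimable adjusted group comparison. The counts (24 to 0, and 13 v 11 to 13 v 0) assume one child and one responding parent per team; the conclusion does not depend on those numbers. It does depend on reading the covariate as required for every outcome and on treating its absence by design as missing.

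The child measures are secondary outcomes. The control-arm gap, however, reaches the adult primary outcomes too, so the repair must cover both. Limiting the questionnaire to adult-reported outcomes would not be enough, because it would stay in group comparisons where control adults have no values.

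**What to change.** Amend Planned Statistical Analyses in two places.

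1. **Child-reported outcomes.** For each one, use one record per child: regress the score at the follow-up being analysed on group, adjust for the child's own baseline score, and leave the Computer Usage Questionnaire out.
2. **Adult-reported outcomes, including the parent-proxy PedsQL.** While control values are absent, do not use the questionnaire in group comparisons. Adjust these for baseline variables measured in both arms, such as the baseline outcome score. Use the questionnaire only as a moderator within the CoEd arm, which fits the aim in Strengths and Limitations of exploring variation in skill among CoEd users.

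The cost is a change of wording. Baseline outcome scores are part of the planned assessments in both arms, so no new data are needed. The downside is small: child and adult outcomes may have different covariate sets, and the group comparison is no longer adjusted for technological skill, which the collected data could not support in any case.

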### Study Overview

We designed a longitudinal, nonrandomized controlled trial to evaluate the impact of the CoEd application developed by our team [36]. We enrolled teams monitoring the school or social inclusion of secondary school pupils with NDD (between 10 years and 16 years old). These teams were recruited throughout France via email communication with schools, school districts, special education advisors, academic inspectors specializing in Special Education, and associations supporting families of children with NDD. Field partners of the project, namely the Nouvelle-Aquitaine academy, Autism Resources Center, and Association pour la Réadaptation et l'Intégration, were also engaged in the recruitment process and encouraged participation in their networks. We also put out calls for participants on digital social networks. Parents, teachers, and health care professionals were asked to complete a questionnaire to check the inclusion criteria. When the participant and child were eligible, all the members of the follow-up team were contacted, and the study was presented to them. Once participation was confirmed, individual participants received a consent form. They were given a week to return the completed form, with researchers available to address any questions during this period.

Whether they were in the control or experimental condition, they had to complete a baseline assessment and a 3-month follow-up assessment, and if they were willing to continue participating, they would complete a 6-month follow-up assessment (Figure 1).

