### Procedure

When the participants were assigned to the CoEd intervention condition, the researchers created the child’s page and the users’ logins on the CoEd application. The participants may provide initial general information to be put on the child’s page by the researchers. At the beginning of the study and after collecting baseline measures, the participants of the CoEd intervention condition received a user manual and video tutorials to help them handle the application, and additional training could be provided by the researchers if needed. Once the study began, the participants were asked to use the application at least once a week but were free to use it as often as they wanted.

The participants from the control group did not receive any intervention and were asked to function as usual.

All questionnaires were administered through online forms. Every participant received an identification number, which was used to anonymize the data collected. At the date of measurement (baseline, 3-month follow-up, 6-month follow-up), participants were instructed by mail to complete the questionnaires. The data collection was monitored by the researchers, and the participants who did not answer were reminded once a week by mail or phone. If participants remained unreachable for more than 6 weeks, they were labeled as “lost” and excluded from the trial.

The data collected through forms and the CoEd application were stored on a secure server at the Inria research center and anonymized using participants’ identification numbers. Only researchers working on the project are authorized to consult the collected data.

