## Results

The study was funded in 2021 with public funds from Conseil Régional d’Aquitaine and the Fondation International pour la Recherche Appliquée au Handicap (FIRAH), Klesia, and Comité National Coordination Action Handicap (CCAH).

Figure 3 shows the flowchart of the recruitment process. We initially recruited 37 eligible teams who were allocated to either the experimental or control group, which resulted in a sample size of 157 participants (2-7 people per team). At baseline, 31 individuals did not complete the questionnaires, leading to the exclusion of 11 teams due to incomplete data. In September 2023, the recruitment ended with 13 teams participating in the experimental condition (n=82) and 11 teams in the control condition (n=45). The experimental group is larger than the control group due to the nature of our action-research approach. Participants and partners expressed a strong preference for being included in the intervention to benefit from the CoEd app, viewing control group assignment negatively. To address this while maintaining rigorous assessment, we included more participants in the experimental group, ensuring sufficient data for analysis and respecting the ethical considerations of action research.

At the end of data collection (June 2024), a total of 59 individuals had dropped out: They stopped responding to the questionnaires and did not reply to our follow-up attempts. Consequently, there were 89 remaining participants at the 3-month follow-up and 67 participants at the 6-month follow-up. Data cleaning and analysis began in March 2025, and results are expected by June 2025. We anticipate that the findings may be ready for publication by the end of 2025, although this timeline remains provisional.

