These secondary indicators address the needs of project stakeholders (inclusive school policymakers, school organizations, teachers, practitioners, parents, and children with SEND) for successful participatory achievements and pave the way for innovative research, such as exploring relationships between CoEd acceptance and effectiveness in inclusive school environments. Most of the participants of this study are people who did not participate in the design steps of the project. Therefore, the bias from “being both designer and evaluator” is limited, and the results from this study will provide insight on the efficacy of using a citizen science approach in the domain of inclusive education. This study combines a traditional top-down approach (ie, expectations relative to specific primary criteria for a prescriptive purpose) with a bottom-up approach driven by the field expertise of the main stakeholders of school inclusion. As a reminder, the study outcomes have been cobuilt thanks to focus group methods involving actual stakeholders as well as researchers in the field (see Multimedia Appendix 2 for details about the focus group sessions). This citizen science approach (albeit risky) contributes to bridging science and practice, facilitating rapid societal impact, and emerging new research issues [64,65]. The results from this study could also contribute to documenting the effectiveness of citizen science and participatory design methods in designing innovative technologies tailored to the specific needs of people, especially in health and disability domains [24,65,66].

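### The user-experience benchmark (RQ4) rests on CoEd users who kept responding, and possibly on some who helped design the app, so it is at risk of upward bias of unknown size

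*Protocol article*

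**What the plan says.** All references are to the Protocol article. RQ4 (Aims) expects the app to give a good user experience and credits the participatory design for this. Under Planned Statistical Analyses, "only the participants of the CoEd intervention condition answered the user experience questionnaire", and the analysis is given in one sentence: "These data will be analyzed through descriptive statistics and compared with questionnaire-related benchmarks". No control comparison and no numerical threshold is attached.

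Three stated rules decide whose ratings are available:

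- Planned Statistical Analyses: "Missing data will result in the exclusion of related observations, and dropouts will be monitored to explore the reasons".
- Procedure, on participants unreachable for more than 6 weeks: "they were labeled as “lost” and excluded from the trial".
- Study Overview, on the later assessment: "if they were willing to continue participating, they would complete a 6-month follow-up assessment".

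Table 1 also lists objective use of the app (openings and posts), "quantified with the following indicators across periods of 3 months or 6 months". On overlap between designers and raters, Strengths and Limitations says: "Most of the participants of this study are people who did not participate in the design steps of the project". It then concludes that this bias is limited, without giving a count or planning an analysis that leaves those people out.

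**The concern.** Each of the three rules selects on continued engagement. People who found the app unhelpful may be more likely to stop answering, and their ratings would then be absent from the mean that is compared with the benchmark. The article supplies part of the reasoning itself. Under Measurement of Technology Experience it links satisfaction of psychological needs through an interface with continued use of it. Under Strengths and Limitations it says that confusion with a governmental tool, and double data entry, could lead some teachers to limit their participation. That burden arises from having to use CoEd.

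RQ4 has no control arm in which similar selection could cancel out. If some raters also helped design the app, their scores could push the mean the same way. At stake is whether a favourable benchmark result describes the app as experienced by those given it, or only by those who carried on with it.

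**Working it through.** **Inputs.** Results section: "13 teams participating in the experimental condition (n=82) and 11 teams in the control condition (n=45)", so 82 + 45 = 127; 89 participants remaining at 3 months and 67 at 6 months, both arms combined; 59 dropouts. Measurement of Technology Experience: the short User Experience Questionnaire is scored from -3 to +3. The article does not give loss by arm, the ratings of leavers or the number of co-designers. The visible text does not say at which follow-up the questionnaire is given, so both are worked.

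**Check of the plan's own figures.** 127 - 59 = 68, against 67 stated. The difference of one is immaterial here; 67 is used.

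**Overall loss.**
- 3 months: 127 - 89 = 38; 38/127 = 29.9%.
- 6 months: 127 - 67 = 60; 60/127 = 47.2%.

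**Bounds on CoEd-arm loss.** The fewest possible CoEd losses arise when as many losses as possible fall among the 45 controls; the most arise when all fall in the CoEd arm.
- 3 months: minimum max(0, 38 - 45) = 0; maximum 38. Range 0/82 to 38/82 = 0% to 46.3%.
- 6 months: minimum 60 - 45 = 15; maximum 60. Range 15/82 to 60/82 = 18.3% to 73.2%.

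Even if every control had left by 6 months, at least 15 of the 82 CoEd users would be missing.

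**Bias in the mean.** Overstatement = (share lost) x (responder mean - non-responder mean). The gap is an assumption; 0 and 0.5-1.5 points are shown.

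| Time | CoEd-arm loss | Gap 0 | Gap 0.5 | Gap 1.5 |
|---|---|---|---|---|
| 3 months | 0% (lower bound) | 0 | 0 | 0 |
| 3 months | 29.9% (if equal in both arms) | 0 | 0.15 | 0.45 |
| 3 months | 46.3% (upper bound) | 0 | 0.23 | 0.70 |
| 6 months | 18.3% (lower bound) | 0 | 0.09 | 0.27 |
| 6 months | 47.2% (if equal in both arms) | 0 | 0.24 | 0.71 |
| 6 months | 73.2% (upper bound) | 0 | 0.37 | 1.10 |

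**Co-designers.** Added overstatement = (their share of raters) x (their mean - the others' mean). With an assumed share of 5% to 30% and an assumed gap of 0.5 to 1.0, this is 0.05 x 0.5 = 0.03 to 0.30 x 1.0 = 0.30. It is zero if no co-designer is in the CoEd arm.

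**The case against.** A reader might infer that the rating will certainly be too favourable. The documents do not show that. Results says only that people stopped responding to questionnaires and follow-up attempts, not that they disliked the app. It also says that assignment to control was viewed negatively, so losses could be concentrated there, and at 3 months the figures allow no CoEd-arm loss at all. This objection stands against any claim of certain direction or known size.

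Four other strong readings also fail:

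- **That co-designers rated the app.** The statement about most participants covers both arms, and no co-designer is placed in the CoEd arm.
- **That log totals over 3 and 6 months will be pooled as if comparable.** No such pooling is planned.
- **That the logs of lost participants will be discarded.** Logs come from the application and do not depend on answering a questionnaire. The exclusion rule simply does not say whether it reaches them.
- **That the benchmark is the whole of RQ4.** Need-satisfaction ratings and log measures also sit under CoEd experience.

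The plan has safeguards: weekly reminders, exploration of dropout reasons, and an explicit acknowledgement of the designer-evaluator problem. One can also argue that response denominators and sensitivity runs belong in an analysis plan. That is fair for the detail. But the exclusion rules are stated here, and nothing stated connects the logs or the dropout reasons to the benchmark comparison. That part of the concern remains.

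**Conclusion.** The point holds as a risk of upward bias of unknown size. It rests on the stated exclusion rules, on overall loss of 30% at 3 months and 47% at 6 months, and on the article's own premise that satisfaction goes with sustained engagement. Because CoEd-arm loss is only bounded, the overstatement for an assumed gap of 0.5-1.5 points is 0-0.70 at 3 months and 0.09-1.10 at 6 months on the -3 to +3 scale. With no gap there is none, whatever the loss. Any contribution from co-designers is additional and equally unquantified. RQ4 is descriptive and separate from the primary and secondary outcomes, so the effect is confined to what may be concluded about user experience. The change is still worth making, because it is cheap and could alter that conclusion.

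**What to change.** For RQ4:

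1. State that the exclusion of lost participants does not apply to log data. Report openings and posts per month of access for all 82 people allocated to CoEd, including those lost.
2. Report the 3-month user-experience scores with the number answering out of 82. The 82 serves as a denominator; scores need not be invented for people who never used the app.
3. Compare log use between responders and non-responders. If they differ, limit the RQ4 conclusion to continuing users.
4. Repeat the benchmark comparison without any CoEd-arm participants who took part in the design steps, and state how many there were.

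Weighting the scores for non-response by log use is optional. With equal loss across arms there would be about 57 responders at 3 months (82 x 89/127) from at most 13 teams, and the weights could be unstable.

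The cost is slightly more analysis of data already held, fewer respondents in the sensitivity run, and a possibly less favourable score.
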